### Economic evaluation

Collected at 6-, 12- and 15-months post baseline assessment:

- Quality of life (EQ-5D-5L and ICECAP-A)
- Use of NHS, local government, third sector and criminal justice services

### The Salvation Army Service observations

Observations will be undertaken by Researchers attending services when collecting other outcome data across both arms to track the context of The Salvation Army services at baseline, 6-, 12- and 15-month follow-ups.

## **14. Statistical considerations**

### **14.1 Sample size**

The unit of randomisation is city/town (the clusters), each cluster will recruit 25 participants (based on maximum possible caseload for each Peer Navigator) in the intervention arm and 30 participants in the control arm. A trial of 20 clusters will recruit 550 participants: we anticipate an attrition rate of up to 40% in the intervention arm and 50% in the control arm, based on feasibility work/related research resulting in outcome data on 300 participants (150 in each arm), equating to mean cluster size of 15. Assuming an ICC of 0.01 this design has 90% power to detect a 0.4SDs effect size. We will work our PPI collaborators to maximise retention in the study, refining processes as we go.

As part of the process evaluation, interviews will be undertaken with staff in the intervention services and with all the 10 Peer Navigators, to understand experiences of, and views on, the intervention from a range of perspectives, and to collect data on changes in the trial contexts during the study:

- Staff in a range of roles in intervention clusters (n=10)
- External stakeholders, including commissioning roles in intervention clusters (n=10)
- Staff in a range of roles in control clusters (n=10)
- Peer Navigators (n=20, i.e., all 10 Peer Navigators at two time points, pre and post intervention)

We will conduct the NoMad questionnaire [40] with a sample of staff (n=4-5) in each intervention setting at three time points (start, middle and end of intervention, aiming for a total sample size of 100-120).

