| Key inclusion criteria             | Individuals attending The Salvation Army Services in one of the 20 included clusters who are over 18 years old; experiencing/at risk of homelessness and self-report problem substance use.                                                                                           |                                                                                                             |
| Planned sample size                | 550 participants will be recruited from 20 clusters for 90% power to detect 0.076 difference on ICECAP-A and 5 on PHQ-ADS at 12-months (assuming an ICC of 0.01 and 40% attrition in the intervention arm and 50% in the control arm).                                                |                                                                                                             |
| Experimental intervention duration | 12 months                                                                                                                                                                                                                                                                             |                                                                                                             |
| Follow-up schedule                 | Participants in the trial are followed up at 6 months, 12 months, and 15 months.                                                                                                                                                                                                      |                                                                                                             |
| Planned trial period               | April 2024 – March 2027                                                                                                                                                                                                                                                               |                                                                                                             |

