### 14.3 Primary outcome analysis

Statistical analysis will be conducted according to a detailed statistical analysis plan which will be finalised prior to the start of data collection. Baseline and outcome data will be described using summary statistics, broken down by group. All analyses will be based on the intention-to-treat principle. Primary outcomes will be analysed using a repeated measures mixed effects linear model extended for cluster randomised trials to include a random effect for cluster and as well as participant [43]. Models will include a fixed effect for treatment, nominal time, country (Scotland/England), and the baseline outcome score. Treatment effects will be estimated at each time point using a treatment-by-time interaction: the primary measurement time point is 12 months after recruitment into the trial. A small sample approximation will be applied to the degrees of freedom given the number of clusters [44].

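### The stated 90% power does not follow from the stated inputs under the small-sample degrees of freedom the protocol requires; without baseline credit they give about 86%

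*Protocol*

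**What the plan says.** Section 14.1 sets out the design. Each intervention cluster recruits 25 participants and each control cluster 30, and "we anticipate an attrition rate of up to 40% in the intervention arm and 50% in the control arm". This leaves "outcome data on 300 participants (150 in each arm), equating to mean cluster size of 15". The conclusion is "Assuming an ICC of 0.01 this design has 90% power to detect a 0.4SDs effect size". The section gives no alpha, no sidedness, no degrees-of-freedom allowance and no baseline-outcome correlation.

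The trial summary in section 1 carries the same figure on the raw scales: "550 participants will be recruited from 20 clusters for 90% power to detect 0.076 difference on ICECAP-A and 5 on PHQ-ADS at 12-months".

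Section 14.3 describes the primary analysis as a repeated measures mixed model with random effects for cluster and participant, and fixed effects for treatment, time, country and baseline outcome score. It adds: "A small sample approximation will be applied to the degrees of freedom given the number of clusters". The type of approximation is not named. Section 14.4 says that treatment effects will be given with 95% confidence intervals and that no adjustment for multiple outcomes is planned.

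**The concern.** Section 14.3 recognises that 20 clusters are few enough to change the reference distribution of the test. The power figure in 14.1 shows no sign of the same allowance: its inputs return 90% when the number of clusters plays no part in the degrees of freedom. The planning figure and the planned test therefore rest on different bases.

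The 90% is a headline property of the design, and a null result would be read against it. If the small-sample basis applies and nothing offsets it, the chance of missing a true effect of 0.4 SD is about 13.5% and not 10%.

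**Working it through.** **Inputs.** From section 14.1: 20 clusters, taken as 10 per arm; 25 × 10 = 250 recruited to intervention, with 40% lost leaving 150; 30 × 10 = 300 recruited to control, with 50% lost leaving 150; 15 analysed per cluster; ICC 0.01; effect 0.4 SD. Assumed: two-sided alpha 0.05. That fits the 95% intervals in 14.4, and it reproduces the stated power where the alternatives do not (one-sided 0.05 gives 94.5%, two-sided 0.025 gives 84.2%).

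**Reproducing the stated figure.**
- Design effect = 1 + (15 − 1) × 0.01 = 1.14. Effective sample size = 150 / 1.14 = 131.6 per arm.
- SE of the difference = √(2 × 1.14 / 150) = 0.1233 SD.
- Noncentrality = 0.4 / 0.1233 = 3.244.
- Normal reference: Φ(3.244 − 1.960) = 90.05%.
- Noncentral t on 298 individual-level degrees of freedom: 89.9%.

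Both round to the stated 90%.

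**Same inputs on cluster-level degrees of freedom.** With 20 clusters the natural value is 20 − 2 = 18, or 17 once country enters as a cluster-level covariate. Using the noncentral t with noncentrality 3.244:

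| Reference | Power at 0.4 SD | Effect with 90% power |
|---|---|---|
| Normal | 90.05% | 0.400 SD |
| t, 18 df | 86.6% | 0.423 SD |
| t, 17 df | 86.4% | 0.424 SD |

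The raw-scale targets imply SDs of 5 / 0.4 = 12.5 for PHQ-ADS and 0.076 / 0.4 = 0.19 for ICECAP-A. At 18 df the effect detectable with 90% power is therefore 0.423 × 12.5 = 5.3 points and 0.423 × 0.19 = 0.080.

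**Sensitivity to the unnamed approximation.** A simulation of the balanced design (200,000 runs) gave 86.6% for a cluster-level t test on 18 df, 85.4% for a mixed model on 18 df with the between-cluster variance bounded at zero, and 86.1% with Satterthwaite-type degrees of freedom. The result does not hinge on one choice.

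**Offset from the baseline score.** If adjustment scales the SE by √(1 − r²), the noncentrality becomes 3.244 / √(1 − r²). The correlation r is an assumption, since the protocol gives none.

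| r | Power, 17 to 18 df |
|---|---|
| 0 | 86.4% to 86.6% |
| 0.3 | 89.3% to 89.5% |
| 0.4 | 91.5% to 91.7% |
| 0.5 | 94.2% to 94.3% |

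Power returns to 90% at r = 0.32 (18 df) or r = 0.33 (17 df).

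**The case against.** The strongest reply is that 86.4% to 86.6% is not the power of the planned test either. Section 14.3 puts the small-sample correction and the baseline score in the same model, and the recalculation counts the cost of the first while giving the second no value. Leaving the covariate out of a planning formula is a common conservative simplification, and a moderate correlation would offset or exceed the loss. This stands. It limits the point to what 14.1 supports, because that section takes no credit for the baseline score and reaches 90% without it.

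A second reply is that 15 per cluster is pessimistic, since 14.1 gives the attrition rates as upper limits. Section 3.1 reports that 30 of the 45 feasibility participants with baseline data also had follow-up, a 33% loss. Attrition of 33% and 43% would give 89.6% to 89.8% on 17 to 18 df, and 30% and 40% would give 90.7% to 90.9%. This is fair as context, but the feasibility data are small and single-arm, and the protocol attaches its 90% to 300 analysed participants.

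Two stronger readings are tempting. A reader might infer that the team used a normal-approximation formula. The protocol names no formula, and a t reference on 298 df reproduces the figure just as well. A reader might also infer that the trial is underpowered. The documents do not show that, because the baseline-outcome correlation is unknown.

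**Conclusion.** The point holds as an unsupported power statement. Under the small-sample degrees of freedom required by section 14.3, the inputs in 14.1 give 86.4% to 86.6% for 0.4 SD, a shortfall of about 3.5 percentage points; equivalently, 90% power applies to about 0.42 SD. This rests on two-sided alpha 0.05, on 17 to 18 as the cluster-level degrees of freedom, and on no credit for baseline adjustment. The first two are assumptions that the protocol does not fix; the third reflects what 14.1 states.

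Severity is minor to moderate. The planned test already uses a small-sample correction, so the analysis itself is not in question. What needs correcting is the stated planning figure and its basis.

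**What to change.** In section 14.1 and the planned sample size entry of the trial summary, state alpha and sidedness and the degrees-of-freedom basis of the power calculation. Then do one of the following:

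- restate power as about 86% for 0.4 SD, saying that no credit is taken for baseline adjustment;
- keep 90% and give the detectable effect as about 0.42 SD (about 5.3 on PHQ-ADS, 0.080 on ICECAP-A), on the same basis;
- keep 90% for 0.4 SD and state the baseline-outcome correlation it depends on (about 0.33 or more), with its source.

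The cost is a wording change in two places. Under the first two options the headline becomes slightly less favourable. No participants, clusters or procedures change.

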### **14.2 Frequency of analysis**

There will be only one final analysis of all outcome data, conducted after the trial is closed to recruitment and the final 12- and 15-month follow-up data have been received. Analyses will only be carried out when all outcome data have been received and the database for follow-up data have been cleaned and locked.

Interim reports will be presented to the Trial Steering Committee and the Data Monitoring and Ethics Committee, containing descriptive information annually (or when requested by the committees). Reports will contain information on recruitment, data collection, safety, and data quality.

### 14.3 Primary outcome analysis

Statistical analysis will be conducted according to a detailed statistical analysis plan which will be finalised prior to the start of data collection. Baseline and outcome data will be described using summary statistics, broken down by group. All analyses will be based on the intention-to-treat principle. Primary outcomes will be analysed using a repeated measures mixed effects linear model extended for cluster randomised trials to include a random effect for cluster and as well as participant [43]. Models will include a fixed effect for treatment, nominal time, country (Scotland/England), and the baseline outcome score. Treatment effects will be estimated at each time point using a treatment-by-time interaction: the primary measurement time point is 12 months after recruitment into the trial. A small sample approximation will be applied to the degrees of freedom given the number of clusters [44].

### 14.4 Secondary outcome analysis

Secondary outcomes will be analysed in a similar way, with generalised linear models appropriate for the distribution of the outcome. All treatment effects will be presented using 95% confidence intervals. We plan no adjustments for multiple outcomes, nor any interim efficacy analysis, only one final analysis.

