### **4.3 Primary objective**

1. Conduct a 2-arm pragmatic cluster RCT (cRCT) across social care homelessness settings in 20 cities/towns in England and Scotland to determine whether the 12-month SHARPS intervention improves mental health and quality of life (co-primary outcomes), compared to standard homelessness care, in adults who are experiencing homelessness and problem substance use.

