## 11.1 Baseline and follow up data

### Primary outcomes

The co-primary outcomes are mental health (compositive measure PHQ-ADS) and quality of life (ICECAP-A) at 12-months.

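### Two co-primary outcomes have no stated success rule, and the stated 90% is power for one outcome only

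*Protocol*

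**What the plan says.** Protocol section 11.1 defines the primary endpoints: "The co-primary outcomes are mental health (compositive measure PHQ-ADS) and quality of life (ICECAP-A) at 12-months". The primary objective (section 4.3) is to determine whether the 12-month intervention "improves mental health and quality of life (co-primary outcomes), compared to standard homelessness care".

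The trial summary gives the sample size as 550 participants from 20 clusters "for 90% power to detect 0.076 difference on ICECAP-A and 5 on PHQ-ADS at 12-months". Section 14.1 supports this with one calculation: outcome data on 300 participants, 150 per arm, mean cluster size 15. It concludes: "Assuming an ICC of 0.01 this design has 90% power to detect a 0.4SDs effect size".

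Section 14.3 describes the primary model. It is a repeated-measures mixed model that includes the baseline score, and "A small sample approximation will be applied to the degrees of freedom given the number of clusters".

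On multiplicity, the only statement is in section 14.4: "We plan no adjustments for multiple outcomes, nor any interim efficacy analysis, only one final analysis". The sentence before it reads "All treatment effects will be presented using 95% confidence intervals". No significance level is stated. Section 14.7, despite its title, sets only cluster-opening and recruitment targets. No section says whether a finding of effectiveness requires both co-primary outcomes or either one.

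**The concern.** The two possible success rules have different operating characteristics. If either outcome is enough and each is tested at 5%, the chance of at least one false positive exceeds 5%. If both are required, no alpha adjustment is needed, but the chance of succeeding on both is lower than the power for each. The protocol fixes no adjustment and quotes one power figure without saying which rule that figure serves. The trial summary joins the two target differences with a plain conjunction, so a reader could take 90% as the chance of detecting both.

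The practical risk is a split result, with one outcome significant and the other not. The protocol alone does not settle how that would be read. Section 7.4 says the statisticians are not blinded to allocation, which is a further reason to fix the rule in advance.

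A second, separate matter is that the power statement does not mention the small-sample degrees of freedom that section 14.3 commits the analysis to.

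**Working it through.** **Inputs from the protocol.** 150 evaluable per arm (250 × 0.6 and 300 × 0.5), mean cluster size 15, 20 clusters (10 per arm), ICC 0.01, effect 0.4 SD, power 90%.

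**Assumptions.** Two-sided 5% per outcome, inferred from the 95% confidence intervals. Correlation between the two test statistics 0 to 0.8, not given. Degrees of freedom 20 − 2 = 18, not given.

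**1. Reproduce the stated 90%.**
- Design effect = 1 + (15 − 1) × 0.01 = 1.14.
- SE of the standardised difference = √(2 × 1.14 / 150) = 0.1233.
- Standardised signal = 0.4 / 0.1233 = 3.244.
- Power = Φ(3.244 − 1.960) = 90.05%.

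The stated figure reproduces as power for one outcome under the normal approximation.

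**2. Either-outcome rule, each at two-sided 5%.** At correlation 0 the family-wise error is 1 − 0.95² = 9.75%. Other values come from the bivariate normal. The last column counts only false claims of benefit.

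| Correlation | Error, either direction | False claim of benefit |
|---|---|---|
| 0 | 9.75% | 4.9% |
| 0.5 | 9.1% | 4.5% |
| 0.8 | 7.8% | 3.9% |

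**3. Both-outcomes rule, by the method behind the stated 90%.** At correlation 0, joint power is 0.9005² = 81.1%. With correlation 0.5 it is 83.3%, and with 0.8 it is 85.7%.

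**4. Separate check: small-sample degrees of freedom.** Replace the normal by a noncentral t on 18 df with noncentrality 3.244 and give no credit for baseline adjustment.
- Per-outcome power = 86.6%.
- Joint power = 75.0%, 78.1% and 81.2% at correlations 0, 0.5 and 0.8.
- 90% per outcome needs a noncentrality of about 3.43, that is 3.43 × 0.1233 = 0.42 SD.

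**5. What baseline adjustment could recover.** Take the variance as reduced by a factor 1 − r², where r is the baseline to 12-month correlation. The noncentrality becomes 3.244 / √(1 − r²). On 18 df:
- 90% per outcome: 1 − r² = (3.244 / 3.43)² ≈ 0.895, so r ≈ 0.32.
- 90% jointly with independent outcomes: each needs √0.9 = 94.9%, a noncentrality of about 3.80. Then 1 − r² = (3.244 / 3.80)² ≈ 0.73, so r ≈ 0.52.

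The protocol gives no value of r.

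**6. Cost of protecting an either-outcome claim.** With 2.5% per outcome (Bonferroni, the first step of Holm), power per outcome on the same inputs is 84.2% by the normal approximation, or 78.0% on 18 df.

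**The case against.** Several points can be made for the protocol.

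- **The statements are compatible.** A reader might infer that no adjustment and 90% power cannot both be right. The documents do not support that. The 90% is correct per outcome. Leaving alpha unadjusted is sound if both outcomes are required, or if each is reported separately without an overall claim. An either-outcome rule keeps at least 90% power (94 to 99% by the normal approximation) and loses only error control. The protocol never claims 5% family-wise error or 90% joint power in so many words. This stands: the defect is the missing rule and the unlabelled figure.
- **The df calculation is one-sided.** A reader might take 75 to 81% as the joint power on the plan's own inputs. It is not. It adds an assumed 18 df and ignores the baseline adjustment planned in the same section. At r = 0.5 on 18 df, power would be 94% per outcome and 89 to 91% jointly. This stands, so the df shortfall is conditional and is kept apart from the main point.
- **The 8 to 10% counts harm as well as benefit.** This is right, and the figure for benefit alone is about 4 to 5%.
- **The no-adjustment sentence sits under secondary outcomes.** This is fair on location, but its wording covers multiple outcomes and the single final analysis generally, and section 14.3 offers nothing else for the co-primaries.
- **The statistical analysis plan may set the rule.** It may, and it is not shown. Two protocol statements would still need attention. A both-outcomes rule would leave the 90% needing a per-outcome label, and an adjusted either-outcome rule would conflict with section 14.4 as worded.

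**Conclusion.** The point holds as a missing decision rule and a power figure that is not labelled as per-outcome. Assuming two-sided 5% per outcome and an outcome correlation of 0 to 0.8, an unadjusted either-outcome claim has a family-wise error of about 8 to 10%. A both-outcomes claim has 81 to 86% power by the plan's own method. The wording of the primary objective leans towards requiring both but does not settle it.

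The degrees-of-freedom point is secondary and conditional. With about 18 df and no baseline credit, power is about 87% per outcome and 75 to 81% jointly. Whether the trial really falls short depends on a baseline correlation that the protocol does not state, so an actual shortfall is not shown. Nor can it be inferred that a split result would be presented as a success, because the unseen analysis plan may prevent that.

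**What to change.** 1. In section 14.3, state the decision rule; the choice is the sponsor's. If both outcomes are required, test each at two-sided 5% with no adjustment and report joint power. If either suffices, use Holm across the two and restate power accordingly.
2. In section 14.4, confine the no-adjustment sentence to secondary outcomes, and state the significance level for the co-primaries in section 14.3.
3. In the trial summary and section 14.1, label the 90% as power per outcome and add the joint figure if both are required. State the assumed outcome correlation, the degrees of freedom, and any baseline to 12-month correlation for which credit is taken, with its source.
4. Make the statistical analysis plan say the same.

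The cost is a wording amendment and a less favourable stated power. No extra participants are needed to describe the design correctly.

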### 14.5 Interim analyses

There are no planned interim analyses, other than the data required for review by the Data Monitoring and Ethics Committee. It is not anticipated that this trial will be stopped early for efficacy or safety reasons.

### 14.6 Handling missing data

The primary analysis will use an unstructured time and covariance structure, which gives unbiased treatment effects when outcome data are missing at random (MAR). A MAR mechanism is unlikely to be the case in this population, and we will explore the impact of missing data using pattern mixture models under missing not random assumptions using models for repeated measures data in cluster randomised trials outlined by Fiero et al. [45].

### 14.7 Success and progression criteria

We have set two targets: one to assess the opening of the clusters as recruitment sites, and the other the recruitment of participants. We propose one decision point at month 10 of the study, to be assessed by the Trial Steering Committee, and our progression criteria are laid out in Table 3 below. We have built contingency into the timetable to take account of unpredictable service demands. There is no internal pilot phase given the short period of recruitment of both clusters and participants.

**Table 2:** Stop/go criteria at 10 months

|                 | GREEN              | AMBER                   | RED                  |
|-----------------|--------------------|-------------------------|----------------------|
| Cluster opening | 100% (20 clusters) | 70-95% (14–19 clusters) | < 70% (<14 clusters) |

|                                 |                               |                                   |                                |
|---------------------------------|-------------------------------|-----------------------------------|--------------------------------|
| Participant recruitment* | 100% (12.5 per cluster month) | 60-96% (7.5–12 per cluster month) | < 60% (<7.5 per cluster month) |
|---------------------------------|-------------------------------|-----------------------------------|--------------------------------|

\* For participants, stop/go will be based on expected number of participants recruited given the number of clusters open to recruitment, to distinguish between cluster- or participant-level barriers to recruitment.

Figure 3 shows the recruitment of clusters and participants over the four-month recruitment phase. Our projection is based upon 20 clusters contributing 25 or 30 participants each over two months. Incorporating a staggered cluster set-up, we would expect to recruit 65 participants in month 7, 500 by the end of month 9, and the remaining 50 in month 10. Recruitment is based upon throughput from our previous feasibility study, use of study-specific researchers to recruit, and having existing ‘pools’ of participants in the cluster services.

**Figure 3:** Recruitment projection

[figure not shown]

To determine success criteria and barriers, we have a risk/mitigation plan with a selection of issues below.

**Table 3:** Risks and mitigations

| Potential risk                                 | How we intend to mitigate risk                                                                                                                                                                                                                                                                                                                                                                                                                                                  |
|------------------------------------------------|---------------------------------------------------------------------------------------------------------------------------------------------------------------------------------------------------------------------------------------------------------------------------------------------------------------------------------------------------------------------------------------------------------------------------------------------------------------------------------|
| Study sites not meeting recruitment milestones | Support of all sites has been secured by The Salvation Army. If there are problems with a particular site, we have resource for extra support to increase recruitment.                                                                                                                                                                                                                                                                                                          |
| Difficulties recruiting Peer Navigators        | We will use learning from the SHARPS feasibility study and work closely with The Salvation Army and our networks to recruit the Peer Navigators. If it is not possible to recruit a Peer Navigator in a cluster (after two attempts of advertising the post) then the cluster will be swapped out of the study and replaced with one of several The Salvation Army clusters that were held as ‘back-pocket’ clusters if needed. The decision on which cluster should act as the |

|                                                                   |                                                                                                                                                                                                                                                                                                                                                                                                                                                                                                                                                                                                                                                                                                                                                                                        |
|-------------------------------------------------------------------|----------------------------------------------------------------------------------------------------------------------------------------------------------------------------------------------------------------------------------------------------------------------------------------------------------------------------------------------------------------------------------------------------------------------------------------------------------------------------------------------------------------------------------------------------------------------------------------------------------------------------------------------------------------------------------------------------------------------------------------------------------------------------------------|
|                                                                   | replacement will be decided based upon the optimal value balance statistics and be agreed with NIHR and our study DMEC.                                                                                                                                                                                                                                                                                                                                                                                                                                                                                                                                                                                                                                                                |
| Peer Navigator(s) leave role early/experiences crises             | We will use our learning from the SHARPS feasibility study and either recruit a new Peer Navigator or identify an alternative solution in response to Peer Navigator challenges, depending on the circumstances and/or when they leave.                                                                                                                                                                                                                                                                                                                                                                                                                                                                                                                                                |
| Data collection issues                                            | Three job share Trial Managers are involved, alongside an experienced (G8) Research Fellow, a (G6) part time Research Assistant who is supporting the process evaluation, and eight Research Assistants to ensure data are collected appropriately, with active support/management from staff within The Salvation Army.                                                                                                                                                                                                                                                                                                                                                                                                                                                               |
| COVID-19 restrictions affecting trial                             | We will put in place mitigations if there are any COVID-19 restrictions that come into place during the trial. This is currently hard to plan for in advance.                                                                                                                                                                                                                                                                                                                                                                                                                                                                                                                                                                                                                          |
| Decommissioning of all The Salvation Army services in one cluster | 
If all of The Salvation Army services within one of the clusters are decommissioned during the 12-month intervention period, we will put in place the following mitigations:
 
 
1) Intervention settings: the Peer Navigator will continue to deliver the intervention to participants in settings outside of The Salvation Army services and the line management of the Peer Navigator will be transferred to the study lead at the University of Stirling
 
2) Control settings: Research Assistants will attempt to follow up control participants and collect data from them in settings outside of The Salvation Army services in public locations such as other homelessness and substance use services in the area
 
 |

